## Objectives {7}

The primary aim of this randomized controlled trial is to determine if the periodized circuit training applied via telerehabilitation is just as effective to the same training applied face-to-face for improving pain intensity and physical function at 14 weeks (primary time-point) and 26 weeks (secondary time-point), in individuals with knee OA.

Secondary aims are to compare clinical (muscle strength and pain catastrophizing) and morphological characteristics (body composition, intermuscular adipose tissue, and muscle architecture), as well effectiveness, adherence, acceptability, and treatment perspectives 14 and 26 weeks after treatment. Safety endpoint will be determined by recording the number of adverse events during the intervention period.

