#### Intervention description {11a}

##### Face-to-face (FtF) circuit protocol

Participants allocated to this group will attend all of their exercise sessions supervised by a trained physical therapist in the Federal University of São Carlos (UFSCar).

The exercise protocol will be performed in a group of up to 5 participants, three times a week, for 14 weeks, totaling 42 sessions [7]. Each session will consist of 5 min of warm-up (stationary bike or walk), circuit protocol, and 5 min of stretching exercises (cool down). Immediately after the warm-up, participants will begin the circuit protocol consisting of exercises for the upper limbs, lower limbs, trunk, and global exercises.

Participants will be instructed to perform each exercise as fast as possible, with the maximum number of repetitions during the time set for the training phase (light, moderate, or intense), in order to ensure the aerobic component [7]. After the first exercise, the participant should move to another station, following a specific order and allowing different muscle groups to alternate between rest and work, favoring recovery and minimizing the risk of muscle fatigue [7].

During the first week of exercise, participants will be familiarized with the equipment and exercises that will be performed during the protocol, performing stratified light exercises, where each exercise should be performed for only 10 s [7]. In the second, third and fifth weeks of training, participants will also perform exercises stratified as light, but each exercise will last 20 s. Moderate exercises will be performed in the sixth, eighth, and ninth weeks, lasting 30 s each. Intense exercises will be performed in the eleventh, twelfth, and fourteenth weeks, lasting 40 s each. The fourth, seventh, tenth, and thirteenth weeks will be considered as regenerative weeks, during which light exercises will be performed for a shorter time (10 s). For all intensities, a maximum transition interval of 30 s between stations will be implemented [7].

The exercises that compound each of the circuit training phases, as well as the execution time are presented in Additional file 1.

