#### Adherence, acceptability, and treatment perspective

Adherence/acceptability to TR, as proposed by Hinman et al. [32] will be assessed by the number of calls received from the lead investigator, as well as the number of sessions per week the participant performed, which should be self-reported during phone calls. The FtF will be evaluated by the number of sessions that the participant attended. In addition, for the same purpose, questions will be asked such as “Do you agree with the proposed exercise plan?” and “Did you perform the exercise program?” Where 0 refers to “strongly disagree” and 10 “strongly agree”. The participants will also qualitatively evaluate the expectation with the result of the exercise protocol, where the scale may vary from “no effect” to “complete recovery” [32]. These outcomes will be self-reported on a paper form only during end-points (14 weeks and 26 weeks).

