## Assignment of interventions: blinding

### Who will be blinded {17a}

The outcome assessors and the data analysts will be blinded to the treatment groups. Due to the nature of the interventions, it will not be possible to blind neither the patients nor the physical therapist responsible to interventions. Thus, it is important to note that the primary outcomes (pain intensity, VAS; and disability, WOMAC function sub-scale), as well as pain catastrophizing, adherence, acceptability and treatment perspective are patient reported, and hence they cannot be blinded.

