### Adverse event reporting and harms {22}

Participants who experience any adverse event are instructed to report these to their physical therapist. All adverse events reported by the participant or observed by the physical therapist during sessions will be recorded. In this RCT, adverse events are defined as any problem experienced during the execution of the study as a result of the assessments, exercise protocol, and/or advice given by the physical therapist.

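### The adverse-event definition requires causality but names no assessor or criterion, so problems considered unrelated fall outside the safety endpoint, and this filter can work differently in the two arms

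*Protocol article*

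**What the plan says.** All places are in the protocol article.

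- **Definition**, Adverse event reporting and harms {22}: "adverse events are defined as any problem experienced during the execution of the study as a result of the assessments, exercise protocol". A problem caused by a therapist's advice also counts.
- **Routes to the record**, same section: "Participants who experience any adverse event are instructed to report these to their physical therapist", and "All adverse events reported by the participant or observed by the physical therapist during sessions will be recorded".
- **Endpoint**, Objectives {7}: "Safety endpoint will be determined by recording the number of adverse events during the intervention period".
- **Blinding**, Who will be blinded {17a}: "it will not be possible to blind neither the patients nor the physical therapist responsible to interventions".
- **Contact in the FtF arm**, Face-to-face (FtF) circuit protocol: participants "will attend all of their exercise sessions supervised by a trained physical therapist", 42 sessions in all.
- **Contact in the TR arm**, Telerehabilitation (TR) circuit protocol: sessions are done remotely. One trained researcher/physical therapist makes recorded calls of about 20 minutes in weeks 2, 3, 4, 6, 8, 11 and 14. The calls also follow changes in symptoms. The interview guide (Table 1) has open questions on the participant's week and wellbeing, but none that asks directly about adverse events.

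**The concern.** Cause is normally judged after an event has been written down. Here it decides whether a problem is an adverse event at all. A problem that someone thinks unrelated is outside the definition, so it is outside both the instruction to record and the count.

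This matters more than usual because the trial compares supervised exercise with the same exercise done alone at home. The problems of most interest when supervision is removed, such as a fall at home, a knee flare some days after a session or chest symptoms, are those whose cause is most arguable.

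Later safeguards are thin. There is no data monitoring committee ({21a}), and the quarterly independent check ({23}) reviews existing documents and source data, so it cannot find a problem that nobody wrote down. At stake is the only safety endpoint the article states. The pain and function outcomes are not affected.

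**Working it through.** The article gives no adverse-event rate and no safety power, so there is no figure of its own to reproduce. The check puts the provisions side by side and then illustrates the mechanism.

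**1. What is counted.** By {22}, adverse event means a problem caused by assessments, exercise or advice. By Objectives {7}, the endpoint is the number of adverse events. Hence the endpoint counts only problems judged to be caused by the trial. The article provides no separate count of other problems.

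**2. Who judges.** {22} names the person who receives reports (the participant's therapist) but not who decides on cause, nor by what criterion. By {17a}, participants and treating therapists know the allocation.

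**3. Whether the filter is the same in both arms.**

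| | FtF | TR |
|---|---|---|
| Scheduled contacts | 3 per week × 14 weeks = 42 sessions | 7 calls |
| Therapist can see a problem during exercise | yes, at every session attended | no, sessions are unsupervised |
| Who first judges cause, for a problem during exercise | therapist or participant | participant |

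The ratio of scheduled contacts is 42 / 7 = 6. For a problem arising outside sessions, the FtF participant faces the same first decision as the TR participant, but has more contacts at which to mention it.

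**4. Illustration (assumed values).** Take 50 participants per arm (Sample size {14}) and the same true proportion r with a problem in both arms. Let a be the probability that a problem is attributed to the trial, and so recorded.

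Recorded = 50 × r × a. The TR-to-FtF ratio is a(TR) / a(FtF), whatever r is.

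| a(FtF) | a(TR) | Recorded FtF v TR, r = 20% | Recorded FtF v TR, r = 40% | Ratio |
|---|---|---|---|---|
| 0.80 | 0.80 | 8 v 8 | 16 v 16 | 1.00 |
| 0.80 | 0.60 | 8 v 6 | 16 v 12 | 0.75 |
| 0.80 | 0.40 | 8 v 4 | 16 v 8 | 0.50 |
| 0.60 | 0.80 | 6 v 8 | 12 v 16 | 1.33 |
| 0.40 | 0.80 | 4 v 8 | 8 v 16 | 2.00 |

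For example, 50 × 0.20 × 0.80 = 8 and 50 × 0.20 × 0.60 = 6. The true numbers are 10 per arm at r = 20% and 20 per arm at r = 40%. So even with equal attribution of 0.80, 2 to 4 participants per arm with a problem drop out of the count.

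**5. Who is still to be recruited.** Implementation {16c} plans stages of 20, 40 and 40. Trial status says that the first two are complete and the last has not started. So 20 + 40 = 60 participants fall under the present definition and 100 − 60 = 40 remain.

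**The case against.** The strongest reply is that safety is descriptive here. The article states no safety hypothesis, margin or test, calls the intervention low-risk ({21a}), and may choose to count intervention-related harms only. Event forms and seriousness grading may sit in a fuller document. Much of this stands: no comparative safety claim is planned, and missing form detail is not the complaint. The definition, however, is stated outright, and applying it as written gives the result above.

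Three stronger readings are tempting, and the article supports none of them.

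- **Different staff judge cause in each arm.** A reader might infer this because FtF sessions have a trained therapist while the TR calls come from one researcher/physical therapist, with adherence measured partly by "the number of calls received from the lead investigator". But no assessor of cause is named for either arm. Sections {11c}, {16b} and {17a} can be read as one therapist role serving both, and {5d} lists 5 physical therapists without assigning them. The remark about the lead investigator concerns adherence, not harms. The asymmetry in the working does not need different staff.
- **Unrelated problems leave no trace.** This is too strong. The TR calls are recorded and follow symptoms, so a problem mentioned there could be heard again if the recordings are kept. Such problems are outside the endpoint, which is not the same as being unrecoverable. The article describes no matching recordings for FtF.
- **The bias favours TR.** Only the choice of assumed attribution rates produces that. Rows 2 and 4 of the second table in the working differ only by swapping the arms.

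**Conclusion.** The point holds in a limited form. The definition makes causality the condition of entry without an assessor or criterion, reports pass through unblinded participants and therapists, and problems considered unrelated are left out of the safety endpoint. This follows from the text alone. That the filter can act differently by arm follows from supervision and contact: 42 observed sessions against unsupervised training with 7 calls.

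Its size cannot be stated. The recorded ratios of 0.50 to 2.00 under equal true rates rest wholly on assumed attribution probabilities of 0.40 to 0.80. They show the mechanism and estimate nothing, and the direction is open.

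The primary non-inferiority conclusions are untouched. As written, though, the adverse-event counts would not support a statement that home training is as safe as supervised training, should a reader draw one from them. The definition should be changed before the last block starts.

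**What to change.** **Adverse event reporting and harms {22}.** Define an adverse event as any untoward occurrence during the intervention period, whatever its cause. Ask about it with the same scheduled question in both arms, for example in the weeks of the TR calls and at the FtF sessions of those weeks. Without this, all-cause counting would still carry the imbalance between 42 sessions and 7 calls. Record relatedness and seriousness as separate fields. Have relatedness judged by an existing team member competent to do so and without access to arm where feasible. The blinded collaborators in Data management {19} are described only as entering and checking data, so their suitability should not be presumed. Some event descriptions will reveal the arm anyway.

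**Objectives {7}.** Report by arm the number of participants with at least one all-cause event, with related events as a second row. Show both by recruitment block, because the first 60 participants were recorded under the present definition. The TR call recordings should not be used to fill in earlier blocks for that arm alone, since this would add a new imbalance.

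**Cost.** A reworded definition, one standard question, two fields on the event form, some assessor time and an amendment through the ethics committee. No extra visits are needed. More minor unrelated events will be logged, and all-cause data will be complete only for the final block of 40 (20 per arm), so that comparison will be imprecise.

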### Frequency and plans for auditing trial conduct {23}

The researchers group meets every week to discuss the trial development and upcoming issues. The study documents, such as informed consents, inclusion and exclusion criteria, and source data are checked four times a year for an independent researcher, who is not involved with the present study. If a document is found to be missing or information is inconsistent, the local ethics committee is notified immediately.

### Plans for communicating important protocol amendments to relevant parties (e.g., trial participants, ethical committees) {25}

All amendments to the protocol will be communicated and approved by the Human Research Ethics Committee from the Federal University of São Carlos-SP.

### Dissemination plans {31a}

The results of this RCT will be disclosed completely in international peer-reviewed journals. Both positive and negative results will be reported. In addition, participants will receive a report with all the results of the study.

## Discussion

Despite the fact that effects of physical exercise on the knee OA population are already widely investigated, the periodized circuit training model is still innovative for treating symptoms and functionality for this population and has resulted in promising findings. In addition, the focus on body composition, especially localized measures such as intermuscular adipose tissue, considering all its associated dysfunctions, such as impairment of muscle architecture and consequent reduction of muscle strength, should be considered in clinical practice, especially when prescribing physical training.

Furthermore, as previously mentioned, there are important barriers in adhering to physical therapy treatment by many patients due to logistical and financial difficulties, especially in developing countries. No studies were found which investigated the effects of remote training, such as telerehabilitation, using a periodized circuit training protocol, compared to face-to-face training in this population, with a randomized controlled trial model.

As previously mentioned, circuit training promotes changes in body composition and muscle strengthening, as well as being a training modality tolerated by patients with knee OA, as attested in our previous studies. The benefits of this modality practiced remotely should be better explored considering its diverse benefits in both skeletal muscle and cardiorespiratory systems. In addition to the physical benefits, it is worth emphasizing the financial benefits that this modality provides, considering the possibility of remote treatments, but still with guidance from the physical therapist.

Given the lack of information in the published literature and the public health impact that exercise intervention protocols can provide, the effects of telerehabilitation using a periodized circuit training protocol on thigh composition (adipose tissue and muscle mass), pain, physical function, muscle architecture, and muscle strength are critical to delineate. Thus, through the study, we hope to provide clinicians with high-quality evidence of treatment for patients with knee OA, providing an effective way to deliver treatment for those who do not have access to face-to-face physical therapy treatment.

This study follows the OARSI recommendations for designing clinical trials for patients with knee OA [21], as well as the SPIRIT recommendations for performing randomized controlled trials [23]. Thus, considering the high prevalence and several disorders related to knee OA, as well as the gaps in the scientific literature regarding telerehabilitation, assessing the efficacy of a periodized circuit training protocol with a design focused on remote rehabilitation, and its impact on body composition, as well as on the several related outcomes, has immediate and high clinical impacts. The results of this study will provide critically needed guidance to the health care system for the treatment and prevention of complications related to knee OA.

Limitations of the study include the fact that before starting the intervention period the participants of the telerehabilitation group will be invited to attend a face-to-face session to clarify questions related to remotely exercises and to provide necessary materials. In addition, exercise participation will be self-reported (as opposed to be measured via accelerometers and similar); therefore, we will not know whether what is reported matches actual participation for the telerehabilitation group.

## Trial status

The protocol was registered on 31 March 2019, under the registration RBR-662hn2. The first two blocks of recruitment, allocation and analysis have already been completed. However, the final block of participants (*n* = 40) did not start yet due to the delay caused by the COVID-19 pandemic. Data recruitment began: 01 April 2019. Data when recruitment will be completed: 30 July 2021 - Version 2 (recruitment date updated - under review).

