### Implementation {16c}

All patients who give consent for participation and who fulfill the inclusion criteria will be randomized. Randomization will be requested by the Trial Coordinator after conclusion of the baseline assessments and after pairing participants (1:1). The estimated time between baseline assessments and allocation will not exceed 7 days. To make RCT feasible, the study sample will be divided into three stages: the first stage will recruit 20 participants (10 per arm), and the second and third stages will recruit 40 participants each (20 per arm), totaling 100 participants.

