## Statistical methods

### Statistical methods for primary and secondary outcomes {20a}

A blinded data analyst will perform all analysis using the Statistical Package for Social Science, version 20.0 (SPSS Inc, Chicago, IL, USA). Baseline characteristics of participants will be presented using descriptive statistics. The between-group differences and 95% confidence interval (CI) for the post-treatment outcomes at 14-week and 26-week end-points will be calculated using mixed linear models using interaction terms of treatment group versus time with no covariate adjustment. Non-inferiority will be demonstrated if the lower bound of the two-sides 95% CI for between-group difference (telerehabilitation minus face-to-face) is above −16 mm in pain intensity and/ or −7.5 units for change in WOMAC physical function subscale at 14 weeks after randomization. Multiple imputation method will be used to impute missing data by using the multiple imputations function in SPSS [57], and an intention-to-treat analysis [58] (including all randomized participants) will be conducted. No adjustments for multiplicity will be made.

It is important to note that, if appropriate, a full statistical plan will be finalized prior to analysis.

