### Interim analyses {21b}

There are no interim analyses planned.

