### Composition of the data monitoring committee, its role, and reporting structure {21a}

A data monitoring committee was not considered as this study adopts a low-risk intervention, and an interim analysis is not planned in this study.

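### Trial status reports analysis of 60 of the 100 participants as completed, against a plan with no interim analysis, while the success rule is still open

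*Protocol article*

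**What the plan says.** Trial status reports that "The first two blocks of recruitment, allocation and analysis have already been completed", and that "the final block of participants (*n* = 40) did not start yet due to the delay caused by the COVID-19 pandemic". Under Implementation {16c} the first stage takes 20 participants, and "the second and third stages will recruit 40 participants each (20 per arm), totaling 100 participants".

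Three other places bear on this:

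- Interim analyses {21b}: "There are no interim analyses planned".
- Composition of the data monitoring committee {21a}: "A data monitoring committee was not considered as this study adopts a low-risk intervention, and an interim analysis is not planned in this study".
- Statistical methods for primary and secondary outcomes {20a}: "if appropriate, a full statistical plan will be finalized prior to analysis".

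The same statistical section states the decision rule. Non-inferiority is shown if the lower limit of the two-sided 95% interval for telerehabilitation (TR) minus face-to-face (FtF) "is above −16 mm in pain intensity and/ or −7.5 units for change in WOMAC physical function subscale at 14 weeks after randomization". No multiplicity adjustment is made.

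**The concern.** Read literally, these statements cannot all be true. If 60 participants have been analysed, there has been an interim analysis. Part of the reason for having no data monitoring committee then falls away, and analysis has come before a plan that was to be finalised ahead of it.

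This matters because two parts of the success rule are not fixed:

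- The and/or wording does not say whether both endpoints must succeed or whether one is enough.
- The rule bounds the difference from below, although the article defines higher VAS and higher WOMAC function scores as worse. It works as a non-inferiority test only if change means improvement, which is not stated.

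Both points have to be resolved before the result can be read. If they are resolved by people who know how the first 60 came out, the rule is no longer prespecified. Blinding the analyst helps only in part, because a comparison of coded arms still shows on which endpoint they differ.

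**Working it through.** **1. How much of the trial is covered.** Stages of 20, 40 and 40 (Implementation {16c}); the last 40 not started (Trial status). Blocks one and two: 20 + 40 = 60, and 60/100 = 60%.

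**2. The plan's own sample size.** Inputs from Sample size {14}: margins 16 mm and 7.5 units, SDs of change 17.9 and 12.12, one-sided 2.5%, 80% power, 18% loss. With a true difference of zero, n per arm = 2 × [SD × (1.960 + 0.842) / margin]².

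- Pain: 19.65, so 20; 20/0.82 = 24.4, so 25.
- Function: 40.99, so 41; 41/0.82 = 50.

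This reproduces 20 and 41, then 25 and 50, and the total of 100.

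**3. Would a comparison on 60 be informative?** Power = Φ(margin / [SD × √(2/n)] − 1.96).

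| n per arm | Pain | Function |
|---|---|---|
| 30 (no loss) | 93% | 67% |
| 24.6 (18% loss) | 88% | 58% |

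So a comparison by arm at this point would say a good deal about the final answer.

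**4. What the and/or choice is worth.** Take the margin direction as corrected, both endpoints truly at the margin, and each tested at one-sided 0.025. The between-endpoint correlation is not in the article, so three values are assumed. The last row is from simulation: the endpoint with the better statistic at 60% is picked, and only that one is tested at the end.

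| Rule at the final analysis | Correlation 0 | 0.5 | 0.7 |
|---|---|---|---|
| Either endpoint suffices | 0.049 | 0.045 | 0.042 |
| Better endpoint at 60% picked, then tested alone | 0.047 | 0.042 | 0.038 |

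At correlation 0 the first row is 1 − 0.975² = 0.0494. If both endpoints are required, the error is at most 0.025 whatever the correlation.

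**5. What the margin direction is worth.** Take raw scores, 41 per arm and the plan's SDs. Suppose TR is observed to be worse by exactly the full margin.

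- Pain: half-width 1.96 × 17.9 × √(2/41) = 7.7; lower limit 16 − 7.7 = +8.3, which is above −16.
- Function: half-width 1.96 × 12.12 × √(2/41) = 5.2; lower limit 7.5 − 5.2 = +2.3, which is above −7.5.

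Both would pass as non-inferior. On raw scores, or on change taken as follow-up minus baseline, the stated bound limits how much better TR may be, not how much worse. If change is defined as improvement, the same rule is correct.

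**6. Cost of requiring both.** At 41 per arm, power is 98.2% for pain and 80.0% for function. Power for both is 0.982 × 0.800 = 78.5% if the endpoints are independent, and at most 80.0% if they are positively correlated.

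**The case against.** The strongest reply is that *analysis* here need not mean a comparison of arms. The article uses the word for measurement elsewhere: the manual segmentation of thigh images, the DXA examination, and the range-of-movement examination on the first assessment day. In a sentence explaining a pandemic delay, recruitment, allocation and analysis can be read as steps of running a block. Two sections say that no interim analysis is planned, and data analysts are to be blinded. This stands: the text does not show that anyone saw comparative results.

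A reader might go further and infer that an unplanned interim look took place, that two looks at one-sided 2.5% raise the overall error to about 4.0%, and that the final test needs a stricter group-sequential level. The documents do not support this. That figure requires that success could have been claimed at 60%, and no early-claim or stopping rule exists. The trial continues to its last 40 participants, and a look with no action does not by itself raise the error rate. Nor would a stricter final level repair a rule chosen after seeing the data.

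It can also be said that much is already fixed: the model, no covariate adjustment, the time point, the numerical margins, intention-to-treat and multiple imputation. That is correct, and covariates are not an open item. A separate analysis plan may also exist. The point is not its absence. The article makes the plan conditional and dates it before an analysis that it elsewhere reports as done.

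Finally, the and/or wording and the margin direction are defects whatever was analysed. That is so, and it is why they should be closed now rather than after the last block.

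**Conclusion.** The contradiction is real on the face of the text and has to be reconciled. It concerns 60 of 100 participants. Whether it reflects loose wording or an undisclosed comparison cannot be decided from the article.

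The consequence is a risk to prespecification, not a calculable inflation from repeated looks. If the choice of endpoint is left open, the one-sided error can reach 4.9% (independent endpoints), or 4.5% and 4.2% at assumed correlations of 0.5 and 0.7. Choosing the endpoint after seeing 60% of the data stays within those ceilings. The margin direction matters more: on raw scores the stated bound would pass a treatment that is worse by the full margin on both outcomes. These figures rest on the plan's SDs and margins, normal approximations and, for the last, 41 evaluable participants per arm.

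**What to change.** - In Trial status, state what was analysed on the first 60, whether by arm, and who saw the results.
- If no comparison by arm was made, replace *analysis* with *assessment* and say so. If one was made, disclose it as an unplanned interim look and confirm that no claim or design decision rested on it. In that case, revisit the reason given for having no data monitoring committee.
- Remove the condition on the statistical plan, so that a plan is mandatory.
- Before stage 3 starts, and before any further comparative analysis, date and lock the success rule: non-inferiority required on both pain and function, which matches the primary aim. Set the direction to the scales: upper limit of the 95% interval for TR minus FtF below +16 mm and below +7.5 units. Alternatively, keep the lower limit and define change explicitly as improvement.

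The cost is a few sentences and an early, dated sign-off. Requiring both endpoints needs no alpha adjustment and leaves power between 78.5% and 80% at the planned 41 evaluable per arm, under independence or positive correlation.
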